### Strategies to improve adherence to interventions {11c}

Following participant randomization, the research team will refrain from implementing specific operational measures to ensure the desired follow-up level. This approach aligns with one of the study’s primary objectives, which is to assess exercise adherence facilitated by gamification. What will be done is to send a standard message weekly to both groups requesting weekly recording of the activity carried out during the week in a spreadsheet.

### Relevant concomitant care permitted or prohibited during the trial {11d}

Participants in the study will be advised against participating in any other exercise programs simultaneously.

### Provisions for post-trial care {30}

The investigators will bear the responsibility of providing assistance to participants who experience any harm during the execution of the protocol.

### Outcomes {12}

Primary outcomes will encompass the following: (1) the concordance between HR and step count measurements assessed by the biosensor under test compared to standard devices (Polar H10 and ActiGraph, respectively); (2) participant perception regarding the utility of the gamified application for exercise engagement; (3) comparison with the prevalence of adherence to the physical activity protocol between the control and intervention groups; (4) evaluation of exercise capacity through ISWT, including stage and the corresponding phase at which the test was halted; and (5) measurement of oxygen consumption (VO_2_).

Secondary outcomes will include the following: (1) tissue oxygenation assessed via near-infrared spectroscopy (NIRS), (2) subjective perception of exertion during ISWT, (3) evaluation of endothelial function, and (4) assessment of autonomic function.

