### Sample size {14}

Since phases 1 and 2 consist of a pilot study for the clinical evaluation of a biosensor prototype and the gamified application that considers a biofeedback system for performing physical exercises, a convenience sample of 15 individuals without medical contraindications for PA will be studied. Assuming a sample loss of 30%, we will recruit 20 participants.

The third phase will be a noninferiority, investigator-blinded randomized clinical trial of the individuals eligible for the study—considering the same eligibility criteria as in phases 1 and 2, in addition to being sedentary—will be divided into two groups: the intervention group (IG), which will receive the exercise protocol through the biosensor and gamified application, and the control group (CG), which will only receive guidelines for performing PA. Considering a confidence level of 95%, power of 80%, ratio of 1:1 between the CG and IG, and estimated prevalence of adherence to the protocol of 70% and 50% for the IG and CG, respectively, it would be necessary to allocate 104 individuals in each group. Adding 30% for possible follow-up losses, 149 sedentary individuals will be assigned to each group, totalling 298 subjects in the study.

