## Statistical methods

### Statistical methods for primary and secondary outcomes {20a}

Data distribution will be assessed using the Kolmogorov–Smirnov test. Parametric data will be presented as mean ± standard deviation, while non-parametric data will be displayed as median (interquartile range). In phase 1, resting and maximum HR assessed by both the Polar H10 monitor and the test biosensor will be compared using either *t*-test or Wilcoxon test, based on data distribution. The same comparison will be applied to the step count measured by the test biosensor and the ActiGraph triaxial accelerometer. Intraclass correlation coefficient (ICC) will also be computed, along with Bland–Altman analysis to assess HR and step count agreement.

During phase 2, a quantitative analysis will be conducted on the frequency of possible gamified application failures. Pre- and post-exercise protocol data, including functional capacity, VO_2_, tissue oxygenation, maximum and resting HR, systemic blood pressure, and perceived exertion, will be compared using *t*-test or Wilcoxon test, based on data distribution. Similarly, the number of steps evaluated by the biosensor under test and the ActiGraph accelerometer will undergo the same analysis, along with ICC calculation.

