For phase 3, a qualitative analysis will be performed on participants’ diary reports and a quantitative assessment of potential gamified application failures. Step count measured by the biosensor will be compared to the ActiGraph accelerometer using Student’s *t*-test or Wilcoxon rank-sum test, depending on residual distribution. Agreement between step counts will be evaluated using Bland–Altman test, Lin’s correlation coefficient, and intraclass correlation coefficient. Pre- and post-exercise protocol data, encompassing functional capacity, VO_2_, tissue oxygenation, maximum and resting HR, systemic blood pressure, subjective exertion perception, endothelial function, and HRV, will be analysed using Student’s *t*-test for paired samples or Wilcoxon signed-rank test, aligned with residual distribution. Participants achieving a minimum of 70% completion of the prescribed protocol will be classified as adherent. As the random allocation is anticipated to ensure baseline comparability between the control and intervention groups, unadjusted analyses will primarily be carried out. In the event of any non-comparability in baseline characteristics due to chance, appropriate adjustments will be made to prevent potential biases. Significance level will be set at *p* < 0.05. The data will be analysed using Statistical Package for the Social Sciences (SPSS) 20.0 (SPSS, Chicago, IL, USA).

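### Five outcomes are called primary without ranking or phase, the randomised phase is sized on adherence alone, and nothing says which result decides the trial

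*Protocol article*

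**What the plan says.** Outcomes {12} begins "Primary outcomes will encompass the following" and lists five items:

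1. concordance of heart rate and step count between the biosensor and reference devices
2. how useful participants find the gamified app for taking up exercise
3. "comparison with the prevalence of adherence to the physical activity protocol between the control and intervention groups"
4. performance on the incremental shuttle walk test (ISWT)
5. oxygen consumption (VO2)

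No item is ranked above another or tied to one of the three phases.

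Sample size {14} plans the randomised phase on an "estimated prevalence of adherence to the protocol of 70% and 50% for the IG and CG", with 95% confidence, 80% power and 1:1 allocation. This gives 104 per group, and 149 per group (298 in total) after a 30% allowance for losses. No other primary outcome enters the calculation.

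Statistical methods {20a} treats the five differently:

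- **Concordance:** intraclass correlation and, in phase 1, "along with Bland–Altman analysis to assess HR and step count agreement", beside a t-test or Wilcoxon test of the device difference. The phase 1 acceptance rule is a standard error within 5%.
- **Perceived utility:** no test is described.
- **Adherence:** a participant is adherent at 70% or more of the prescribed protocol.
- **ISWT capacity and VO2 in phase 3:** "Student’s *t*-test for paired samples or Wilcoxon signed-rank test, aligned with residual distribution", applied to pre- and post-protocol data.

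One level covers everything: "Significance level will be set at *p* < 0.05". Section {20c} applies intention-to-treat to the primary outcomes, in the plural.

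**The concern.** The outcome list, the sample size and the significance level do not fit together. The list gives several outcomes equal standing, the sample size serves one, and the significance rule does not separate them.

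Phase 3 could end with adherence no different between groups and a significant change in VO2. As written, that could be reported as success on a primary outcome, although adherence is the only outcome the trial was sized for. A stricter reader could require all the phase 3 primaries to succeed and call the same trial negative. Under the first reading the error rate over the primary outcomes is not held at 5%. Under the second, the planned power does not describe the chance of success. The article's Discussion expects a successful trial to inform public health decisions, so what counts as success should be settled beforehand.

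**Working it through.** **Step 1. Reproduce the plan's figure.** Inputs from Sample size {14}: p1 = 0.70, p2 = 0.50, power 80%. The 95% confidence is read as two-sided alpha 0.05. Mean proportion 0.60, difference d = 0.20.

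Without continuity correction:

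n = [1.960 × √(2 × 0.60 × 0.40) + 0.8416 × √(0.70 × 0.30 + 0.50 × 0.50)]² / 0.20²
= (1.3579 + 0.5708)² / 0.04 = 93 per group.

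With continuity correction:

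n' = (n/4) × [1 + √(1 + 4/(n × d))]² = (93/4) × [1 + √(1 + 4/18.6)]² = 102.8, so 103 per group.

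The plan states 104, a difference of one. One-sided versions give 74, or 83 with correction, and do not fit. Losses: 104/0.70 = 148.6, so 149; 2 × 149 = 298. The sample size is therefore that of a two-sided comparison of adherence, with the whole 0.05 spent on it.

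**Step 2. Count the primary outcomes that could yield a claim about the exercise programme in phase 3.**

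| Outcome | Analysis described | Counted? |
|---|---|---|
| Concordance | Agreement statistics, test of device difference | No |
| Perceived utility | No test | No |
| Adherence | Comparison of groups | Yes |
| ISWT capacity | Paired pre/post | Yes |
| VO2 | Paired pre/post | Yes |

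This leaves three.

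**Step 3. Error rate if any one of the three suffices.** Each is tested two-sided at 0.05 and each null hypothesis is true.

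Independent tests: 1 − 0.95³ = 0.143.

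The documents give no correlations, so a range is assumed. Simulation of equally correlated normal test statistics, 1,000,000 draws:

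| Assumed common correlation | At least one false positive |
|---|---|
| 0 (exact) | 14.3% |
| 0.3 | 13.6% |
| 0.5 | 12.6% |
| 0.7 | 10.9% |
| 0.9 | 8.4% |

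With 0.7 between ISWT and VO2 and 0.3 between each of them and adherence, the result is 12.6%. Every scenario is above 5%.

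**Step 4. Power if all three are required.** The chance that all succeed cannot exceed the chance that adherence succeeds, so 80% becomes an upper limit. The shortfall cannot be computed, because no effect size or standard deviation is given for ISWT or VO2.

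**Step 5. Cost of keeping three primaries with an equal split of alpha.** Alpha per test is 0.05/3 = 0.0167. The Step 1 formula with continuity correction then gives 135 per group for adherence, and 135/0.70 = 192.9, so 193 after losses. With 104 evaluable per group, power for adherence (without continuity correction) falls from 84% to 71%.

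**The case against.** **A family of five.** A reader might infer that all five outcomes are tested at 0.05 and put the error rate at 1 − 0.95⁵ = 22.6%. The document does not support this. Perceived utility has no stated test. Concordance is mainly an agreement analysis with its own acceptance rule; its heart-rate part belongs to the small pilot sample, and a significant device difference counts against the biosensor. Pooling these with the randomised comparison has no clear meaning.

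**Three between-group tests.** A reader might also infer that ISWT capacity and VO2 are specified as comparisons between groups. Other sections lean that way: both arms are assessed before and after the 6 weeks, and block randomisation is justified by variability in VO2. But the statistical section names only paired pre/post tests for them. Adherence is the only primary outcome worded as a comparison of groups. This objection stands, and the error rates above are conditional on any of the three being claimable.

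**The document points to adherence.** It is the sole basis for the sample size, it has an explicit definition, section {11c} calls its assessment one of the primary objectives, and the phase 3 benchmark is 70% adherence. This is fair and supports choosing adherence. It does not rank the outcomes, and the benchmark governs continuation.

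**Multiplicity detail belongs in the analysis plan.** True of the choice between Holm and a fixed order, and the absence of either is not the point here. Which outcomes are primary is fixed in this article, and that designation is what does not fit the sample size.

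**Conclusion.** The point holds in limited form. Five outcomes carry equal primary status without rank or phase, the randomised phase is sized on one of them, and no rule says which result decides the trial.

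If a claim could rest on any of adherence, ISWT capacity and VO2 at an unadjusted 0.05, the chance of at least one false positive is 14.3% under independence and about 8% to 14% at common correlations of 0.9 to 0.3. If all three were needed, the stated power covers adherence only.

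These figures assume a family of three, two-sided tests of no difference or no change, each of size 5%, and assumed correlations. If the paired tests were run separately in each arm, there would be 1 + 2 × 2 = 5 tests and a higher rate; the text does not say whether they will be. The trial is also called noninferiority while its sample size uses a difference and no margin. That is a separate matter and does not enter this calculation.

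The point should be corrected before analysis. It does not call the size of the trial into question.

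**What to change.** In Outcomes {12}:

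- Name the between-group comparison of adherence as the only primary outcome of phase 3.
- Make ISWT capacity and VO2 secondary outcomes of phase 3.
- Label device concordance as the primary outcome of phase 1.
- Label perceived utility as descriptive.

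In Statistical methods {20a}, state that ISWT capacity and VO2 will be compared between groups, either in a fixed order or with Holm's procedure. To hold the error rate over all three at 5%, proceed to them only if adherence succeeds.

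The cost is wording, and ISWT capacity and VO2 lose primary status. The 104 and 149 per group stand, because adherence keeps the full 0.05.

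If the investigators wish to keep all three as primary, a written decision rule would also resolve the ambiguity, at a higher price. Success on any one with an equal split of alpha needs 193 per group after losses, or 2 × 193 = 386 in total against 298, and that covers adherence only. Success on all three needs power calculations for ISWT and VO2 that the article does not contain.

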### Participant timeline {13}

After randomization, participants will perform the initial assessment and in the following 6 weeks will perform the exercise prescribed according to the allocation group. After 6 weeks, the assessment will be repeated and participation in the study will end. The chronological schedule for participants can be found in Fig. 2.

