**Fig. 1 Fig1:**
[figure not shown]
Flow Chart of participants. Asterisk (*) symbol indicates the following: from the 2875 individuals interviewed using the IPAQ, those identified as sedentary will undergo our eligibility screening. Subsequently, the qualified participants will be randomized

This study received approval from the Research Ethics Committee of UFCSPA prior to data collection, with registration number 54492221.80000.5345. The research team assumes responsibility for ensuring the integrity of this study.

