### Phase 3: Evaluation of gamified in uncontrolled environment

Phase 3 comprises a noninferiority, investigator-blinded, randomized clinical trial with two distinct groups: the intervention and control groups. Participants within the intervention group (IG) will install the gamified application on their smartphones and use a biosensor during exercise sessions. These sessions will align with the prescribed intensity derived from the ISWT, following the 6-week regimen detailed in phase 2. Participants will be duly instructed to cease exercising if they experience symptoms like chest pain, discomfort, or dizziness.

Within the gamified application, participants will have access to a diary feature, enabling them to log notifications received and their efforts during exercise, both monitored by the biosensor and the gamified app. On the other hand, individuals in the control group (CG) will receive instructions to engage in physical activity at home without biosensor monitoring. They will use the app independently, aiming for a minimum of 300 min per week at moderate intensity or at least 150 min per week at vigorous intensity (self-assessed).

Preceding and following the 6-week period, both the IG and CG will undergo assessments akin to those conducted in phase 1. These include evaluations of functional capacity, muscle oxygenation, and further assessments led by trained and blinded researchers.

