### Implementation {16c}

Notably, the researcher entrusted with generating the allocation sequence will remain uninvolved in participants’ data collection. Additionally, the investigator responsible for conducting the functional assessments will be kept blind to the participants’ allocation status.

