## Assignment of interventions: blinding

### Who will be blinded {17a}

Owing to the nature of our intervention, which encompasses physical activity and gamification, participant blinding will not be feasible. However, the researcher overseeing the evaluation process will be kept blinded.

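### Phase 3 baseline testing is scheduled after randomisation in a trial without participant blinding, and nothing says the arm is withheld until baseline is complete, so baseline ISWT and VO2 are open to allocation effects

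*Protocol article*

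**What the plan says.** All references are to the protocol article.

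- **Order of events.** Participant timeline {13} sets the sequence as follows: "After randomization, participants will perform the initial assessment and in the following 6 weeks will perform the exercise prescribed according to the allocation group". The Fig. 1 caption is compatible with this. It moves from IPAQ interview to eligibility screening and then says "Subsequently, the qualified participants will be randomized", with no baseline assessment named in between.
- **Content of the assessment.** The Phase 3 section: "Preceding and following the 6-week period, both the IG and CG will undergo assessments akin to those conducted in phase 1". Phase 1 assessments include the ISWT with VO2 and perceived exertion.
- **Status of these measures.** Outcomes {12} lists as the fourth primary outcome "evaluation of exercise capacity through ISWT, including stage and the corresponding phase at which the test was halted", and VO2 as the fifth. Perceived exertion is secondary.
- **Blinding.** Who will be blinded {17a} says that "participant blinding will not be feasible". Implementation {16c} says that "the investigator responsible for conducting the functional assessments will be kept blind to the participants’ allocation status". Concealment mechanism {16b} specifies sealed envelopes but not when they are opened.
- **Use of baseline.** Statistical methods {20a} says that the phase 3 pre and post data "will be analysed using Student’s *t*-test for paired samples or Wilcoxon signed-rank test, aligned with residual distribution". Analyses are mainly unadjusted, with adjustment if chance leaves the arms unbalanced at baseline. The ISWT also sets the intervention group's exercise intensity (Phase 3 section, with the heart rate reserve calculation in the phase 2 prescription).
- **Analysis set.** Section {20c} plans intention-to-treat on all randomised participants for the primary outcomes.

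**The concern.** A baseline protects a comparison only if allocation cannot have influenced it. The safe ways to secure this are to measure it before randomisation or to keep the arm hidden until it has been measured. The article states the reverse of the first and is silent on the second.

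Three consequences follow if participants learn their arm before testing.

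1. How far someone walks in the ISWT depends partly on effort. Disappointment or enthusiasm about the arm can change that effort, and any baseline shift feeds directly into the measured change.
2. Attendance at baseline can depend on the arm. A person who is randomised and does not attend has no pre value, so the paired analysis of ISWT and VO2 cannot include all randomised participants without some assumption about the missing value.
3. In the intervention group the heart rate reserve uses the maximum heart rate reached in the functional test. A change in effort would therefore also alter the prescribed intensity, not only the measurement.

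The plan to adjust for chance imbalance is weakened as well. An imbalance that arises after a known allocation need not be chance, and adjusting for it conditions on something allocation may have affected.

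**Working it through.** **Step 1: is there text that rescues the order?** Four places bear on it.

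| Section | What it settles |
|---|---|
| Participant timeline {13} | Initial assessment follows randomisation |
| Fig. 1 caption | Screening, then randomisation; baseline not mentioned |
| Phase 3 section | Assessment precedes the 6 weeks; silent on its order relative to randomisation |
| Concealment {16b}, Implementation {16c}, Blinding {17a} | Envelopes, blinded assessor, unblinded participants; time of disclosure not stated |

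Only {13} fixes the order, and nothing contradicts it. The Phase 3 wording would fit either order. Fig. 2, the schedule, is not available in the text reviewed.

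**Step 2: does anything need this order?** Sequence generation {16a} names age and gender as the factors to balance. Both are known without an ISWT, so randomisation could wait until baseline is finished.

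**Step 3: is the sample size involved?** Inputs from Sample size {14}: adherence 70% and 50%, 95% confidence, 80% power, 1:1.

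- Uncorrected: n = [1.960·√(2·0.6·0.4) + 0.842·√(0.7·0.3 + 0.5·0.5)]² / 0.2² = 93 per arm.
- With continuity correction: (93/4)·[1 + √(1 + 4/(93·0.2))]² = 102.8, so 103, against 104 stated.
- Losses: 104/(1 − 0.30) = 148.6, so 149 per arm; 2 × 149 = 298.

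The stated figures reproduce to within one person per arm. They rest on adherence, which has no baseline value, so re-ordering the visit leaves them unchanged. The loss allowance is 149 − 104 = 45 per arm. The article does not say how many of these losses might fall between allocation and baseline.

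**Step 4: how would a shift propagate?** Let one arm's baseline be displaced by s (in SD units) because of allocation, with no true effect and no displacement at follow-up. Let r be the pre-post correlation, with equal SDs.

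- Mean within-arm change, which the named paired tests examine: biased by s in the displaced arm.
- Between-arm difference in change: bias s, standard error √(2(1 − r))·√(2/n).
- Baseline-adjusted difference (ANCOVA): bias r·s, standard error √(1 − r²)·√(2/n).

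**Step 5: illustration.** The article gives neither s nor r, and it names neither a between-arm change score nor ANCOVA for these outcomes. Everything here is assumed: n = 104 per arm, two-sided 5%, r from 0.5 to 0.8.

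With m = bias/standard error, the false-positive rate is 1 − Φ(1.96 − m) + Φ(−1.96 − m). Example with r = 0.5, s = 0.2: standard error 1 × √(2/104) = 0.139, m = 1.44, rate 30%.

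| Shift s | Change score, r = 0.5 to 0.8 | ANCOVA, r = 0.5 to 0.8 |
|---|---|---|
| 0 | 5% | 5% |
| 0.1 SD | 11–21% | 7–16% |
| 0.2 SD | 30–63% | 13–49% |
| 0.3 SD | 58–93% | 24–82% |

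Baseline adjustment reduces the bias but does not remove it.

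**The case against.** The strongest reply is that the article does not say participants know their arm at baseline. Section {17a} says only that blinding is not feasible given the nature of the intervention. The time at which the envelope is opened is not given, and the schedule figure cannot be read here. Disclosure after the baseline test is compatible with the text. This stands: a reader might infer that participants certainly know their arm when tested, but the documents support only that they may. Disclosure after baseline would deal with effort, but not with people lost between randomisation and testing.

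Two further inferences go too far.

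- **That early losses leave no usable data.** Adherence needs no baseline value. The control group records it weekly, and an intervention participant who never starts could be counted as non-adherent. Only the pre/post outcomes lose data.
- **That the first test will expose ineligible people who are already randomised.** The Fig. 1 caption places eligibility screening before randomisation, and no criterion in {10} is a threshold on ISWT or VO2. An exercise test might reveal exertional angina, which is an exclusion, but that is thin ground.

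It can also be said that phase 1 uses the better of two ISWTs. If phase 3 does the same, a single poor effort matters less. A systematic difference between arms would remain, and two tests up to a week apart would lengthen the interval in which allocated participants can be lost before baseline is complete.

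Finally, the table above concerns analyses the article does not name. That limits the quantification, but a displaced baseline also distorts the paired comparison the article does name.

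**Conclusion.** The point holds in limited form. The article fixes baseline after randomisation, does not blind participants, and does not say that the arm is withheld until baseline is complete. The order therefore permits effort and attendance to differ by arm at baseline. Exposed are the pre/post and any baseline-adjusted comparisons of ISWT and VO2, the secondary perceived exertion measure, and the ISWT-derived intensity in the intervention group. Assessor blinding protects the scoring only.

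Neither the size nor the direction of any bias can be derived from the document; the rates shown depend entirely on the assumed shift and correlation. The adherence outcome and the sample size built on it are not affected by a baseline effort shift. This is a weakness that should be corrected because correction is cheap, not evidence that the trial's results will be biased.

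**What to change.** Reverse the order in Participant timeline {13}. After eligibility screening, complete all baseline assessments, including both ISWTs if two are done as in phase 1. Then randomise, with someone other than the blinded assessor opening the sealed envelope, and start the 6 weeks from there. Bring the Fig. 1 caption and the schedule into line.

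If that order cannot be adopted, state at the least that allocation stays concealed from both participant and assessor until baseline is complete. This protects effort, but people lost between randomisation and baseline would still lack a pre value.

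The cost is small. No procedure is added and the sample size is unchanged. A few people will be tested and then not randomised.
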